### Objective

We aim to investigate the effect of a Transfer Intervention Procedure (TIP) on the time between hospital discharge and the time when the medical, medication and nursing handovers are being sent to the next health care provider. Our goal is to reduce this time to 24 h after hospital discharge for all patient handovers. Also, we aim to reduce length of hospital stay and unplanned readmission within 30 days rates.

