### Primary and secondary outcomes

The primary outcome is the number of medical, medication and nursing handovers being sent within 24 h after discharge. Secondary outcomes are length of hospital stay unplanned readmission within 30 days rates.

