### Patients and sample size

All patients over the age of 18 admitted for more than 48 h to one of the 16 participating wards of the eight participating hospitals are eligible for inclusion. The aim is to include at least 22 patients at each time point in all participating hospitals; 11 patients from an internal ward and 11 patients from a surgical ward. With a total of six time points, this will result into at least 65 patients per ward. Hence, we will include at least 1000 patients in the period prior implementation (baseline group) and 1000 patients in the period after the implementation (intervention group). This number is based on the number of hospital beds at the participating wards and feasibility with regard to data collection. We conducted a power analysis with this number of patients, which is based on the findings of a previous study [16]. However, we expect to find a greater effect in the current study, namely a reduction of 78 % in the time of patient handovers being sent to the next health care provider. In a simulation study with 16 wards, each contributing 65 patients, we estimated the power to be approximate 91 % to demonstrate a reduction of 78 % in time until sending the medical discharge letter, assuming that the intraclass correlation coefficient does not exceed 0.05.

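### The only stated power, 91%, is for the medical discharge letter, so no stated power applies to the primary outcome, which covers three kinds of handover

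*Protocol article*

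**What the plan says.** Under *Primary and secondary outcomes*: "The primary outcome is the number of medical, medication and nursing handovers being sent within 24 h after discharge". The abstract repeats this definition. The *Objective* sets the 24 h goal "after hospital discharge for all patient handovers", and the *Discussion* aims for all three kinds to be sent in that time without exception.

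The section on the intervention itself (*The transfer intervention procedure*) breaks the patient handover down into a medical, a medication and a nurse part.

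*Patients and sample size* first gives the expected effect in general terms, as "a reduction of 78 % in the time of patient handovers being sent to the next health care provider". The next sentence reports a simulation of 16 wards with 65 patients each and an intraclass correlation of at most 0.05. There the power of about 91% is for a 78% reduction "in time until sending the medical discharge letter". This is the only power figure in the article. The same section says that the number of patients came from bed numbers and feasibility.

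Table 2 (*Data collection*) records the time in hours from discharge to the medical, medication and nursing handovers.

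**The concern.** Within two sentences the power paragraph moves from patient handovers in general to one document, the medical letter. A reader who takes 91% from it will naturally attach it to the primary outcome, but that outcome also contains the medication and nursing handovers, and nothing was simulated for them or for the three together.

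What is at stake is how the main result is read. Suppose the medication and nursing handovers respond less than the letter. A real gain in letters could then be diluted in a combined result, and a null finding would be taken to come from a test with 91% power. The reverse is also possible: if all three respond alike, combining them may give more power than stated. As written, the article does not let the reader tell which applies.

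**Working it through.** **1. The plan's own figure.** The sample arithmetic agrees: 11 × 6 = 66 patients per ward (stated as at least 65), and 16 × 65 = 1040 per period (stated as at least 1000).

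The 91% can be neither reproduced nor refuted, because the article gives no baseline time, spread, significance level or simulated model. As a check, take log time, a two-sided 5% level and a log ratio of −ln(1 − 0.78) = 1.514. The log-SD that yields 91% is 1.514 / [3.30 × √(2/n)], where n is the effective number per period:
- 1040/0.95 = 1095 (within-ward comparison): 10.7
- 1040/4.2 = 248 (design effect 1 + 64 × 0.05 = 4.2): 5.1
- 520/0.95 = 547 (65 per ward in total, within-ward): 7.6
- 520/4.2 = 124 (65 per ward in total, design effect 4.2): 3.6

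The result depends wholly on inputs that are not shown. The mismatch does not depend on this step.

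**2. Side by side.**

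| | Primary outcome | Power statement |
|---|---|---|
| Handovers covered | medical, medication, nursing | medical letter |
| Measure | number sent within 24 h | time until sent |

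The first row is the point here. The second row is a separate difference, but it means that even the medical part is not on the scale of the primary outcome.

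**3. How far power could move if the three are pooled.** Nothing below is power for the primary outcome; it only shows sensitivity. Assumptions, none of them in the article: two-sided 5%, equal weights, equal variances, common correlation ρ, and an effect on each of the other two handovers equal to g times the letter's. At 91% power the letter has z = 1.960 + 1.341 = 3.301. Then

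pooled z = 3.301 × [(1 + 2g)/3] / √[(1 + 2ρ)/3], and power = Φ(pooled z − 1.960).

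| g | ρ = 0 | ρ = 0.5 | ρ = 1 |
|---|---|---|---|
| 1 | 100% | 98% | 91% |
| 0.5 | 97% | 77% | 60% |
| 0.25 | 82% | 52% | 38% |
| 0 (equal-variance worst case) | 48% | 27% | 20% |

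**4. Relaxing equal variances.** If the other two do not improve because they are nearly always on time, they also vary little, so the last row above overstates the loss. Take the letter at 50% on time (variance 0.25) and the other two unchanged at 97% (variance 0.97 × 0.03 = 0.0291 each), with the same z for the letter. Pooled z = 3.301 × 0.5/√V, where V is the variance of the sum of the three.
- Uncorrelated: V = 0.25 + 2 × 0.0291 = 0.3082, z = 2.97, power 84%.
- Largest feasible correlations (covariance 0.5 − 0.5 × 0.97 = 0.015 with the letter, 0.0291 between the other two): V = 0.3082 + 4 × 0.015 + 2 × 0.0291 = 0.4264, z = 2.53, power 71%.

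The same steps give 80% and 61% with the other two at 95%, and 89% and 84% at 99%.

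**5. If the three are not pooled.** Suppose each handover had 91% power.
- All three must succeed: 0.91³ = 75% if independent, up to 91% if perfectly correlated.
- Each tested at 0.05/3 (critical value 2.394): Φ(3.301 − 2.394) = 82% per handover.

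**The case against.** The strongest objection is that the planning effect does cover all three. The article's own breakdown of the handover includes medication and nursing, and the 78% is stated for handovers in general. That is g = 1 in the table, where pooling loses nothing. This stands, and it rules out saying that the other two have no planning effect. It does not supply a power figure, because the simulation used only the letter.

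A reader might infer that the true power is 20% to 48%, or simply that the study is underpowered. The article does not support either. Those figures need a pooling rule it does not state, no effect at all on two of the three handovers, and equal variances. The last of these fits poorly with the likeliest reason for no effect, namely that those handovers are already prompt. Nor does the article say that they are prompt; its *Background* says only that handovers are often delayed.

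It can also be said that the three may be analysed separately, that the rule for combining them may belong in an analysis plan not shown here, and that the power sentence already names the letter. All fair, so the missing rule is not itself a finding. What remains is narrower: the article prints one power figure, and it is for something other than the outcome it calls primary. Finally, feasibility set the sample size, so the point changes how the result is read and not the number of patients.

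**Conclusion.** The point holds as a mismatch between two statements in the article. The 91% describes time to the medical letter, the primary outcome covers three handovers, and no stated power applies to the latter. This rests on the text alone and is true whether the three are pooled, all required or analysed separately.

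Its size cannot be fixed. Power for the primary outcome may be above or below 91%, depending on the effects on the other two handovers, their variances and correlation, and how the three are combined. Under equal weights and equal variances it is 91% or more if all three improve equally, and it falls as the other two lag. A loss of power is possible but not shown. The correction is worth making because it is cheap and affects how a null result would be read.

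**What to change.** In *Patients and sample size*, say explicitly that the 91% is for time to the medical discharge letter and is not the power of the primary outcome.

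Re-run the simulation for the primary outcome as it is defined. State the assumptions for each of the three handovers and the way they are combined, show the result as a range, and quote that as the power for the primary outcome. Because that outcome counts handovers sent within 24 h, the same run also removes the difference in scale.

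Report the medical, medication and nursing handovers as separate series beside any combined result, so that the comparison that was powered is visible.

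The cost is a re-run of an existing simulation, a few sentences and additional series from times that Table 2 already collects. The re-run needs planning values for medication and nursing handovers that the article does not give, so these must be assumed openly. No extra patients are needed. The downside is that the stated power may become less favourable.

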### Segmented regression of interrupted time series analysis

We will use segmented regression methods for analyzing the data, which is most commonly used to assess ITS data as it allows assessing how much an intervention changed a certain outcome immediately and over time [13]. We will use segmented regression analysis to assess significance of changes in level and slope of the regression lines before and after implementation of the TIP procedure. We will collect data 6 months prior to implementation of the intervention and 6 months after implementation. We will adjust for autocorrelation, which refers to the serial dependence of outcome measure error terms, in order to avoid underestimating standard errors and overestimated significance of the effects of the TIP procedure [14]. We will consider non-stationary data, taking into account other interventions implemented in the same period or changes in hospitals’ policies.

### Qualitative evaluation of patient satisfaction and facilitators and barriers of implementation

In addition to quantitative data collection, comprehensive qualitative data regarding the implementation of the intervention may provide valuable additional information when an implementation evaluation is conducted [13]. First, in order to evaluate patient satisfaction and the patient’s perspective on the discharge procedure, semi-structured interviews will be conducted with patients shortly after discharge. Question will be asked regarding their experience with the discharge procedure. For example, patients will be asked whether they felt confident about returning home and if they felt they were well informed. Also, their opinion with regard to the discharge conservation and personalized patient discharge letter (PPDL) will be assessed. Post-implementation, RS will interview patients until saturation of the data emerges [17].

Second, one focus group discussion will be conducted with the project leaders of all participating hospitals and eight focus group discussion will be conducted with the project groups of each hospital. These group discussions will be used in order to reflect the social and cultural context of barriers and facilitators to implement the TIP and improve the discharge process in the hospital. The project leaders are, together with their project group, responsible for local implementation of TIP. The project groups consist of the project leader and, for example, the head of the participating ward, a senior nurse and physicians. An experienced moderator (RS) will lead all focus group interviews.

The interviews and focus groups will be recorded, after written consent is obtained from the participants, and transcribed verbatim. Data derived from the interviews with patients and focus groups discussions with professionals will be analyzed iteratively, consisting of a combination of open coding and sensitizing concepts by which constant comparisons are made [18, 19]. MAXQDA Software will be used in order to facilitate the coding process of both the semi-structured interviews with patients and the focus group discussions.

### Validation and process evaluation

In order to assess compliance of the professional with the TIP, we will evaluate the percentages of compliance with regard to process indicators on the checklist, including discharge planning within 48 h, start with arrangement of required aftercare within 48 h (if needed), holding a discharge conversation within 12 to 24 h before discharge and providing a patient letter. Also, in order to determine whether there is any compliance with regard to these process indicators prior to implementation of the TIP procedure, the number of patients for whom these aspects of the TIP procedure were done will be considered.

## Discussion

This study protocol describes the design, implementation and evaluation of the Transfer Intervention Procedure (TIP); a discharge bundle to improve discharge care on an organizational level. We aim for a one hundred percent of medical, medication and nursing handovers being sent within 24 h to the next health care provider. Yet at the same time, professionals should be aware that this does not come at the expense of the content of the patient handovers. To our knowledge this is the first study that investigates the implementation of such a discharge bundle on a large, national-scale, in eight different Dutch hospitals. If effective, nationwide implementation of the discharge bundle may result from this study protocol.
